## **5.8 Study intervention and termination**

All eyedrops (0.01% atropine sulfate, 1% hydroxypropyl methylcellulose) will be prepared in the same single-dose package without preservative, with the same solvent (1% hydroxypropyl methylcellulose). Participants will receive one drop in each eye once per night.

The single-dose containers of eyedrops will be stored in the area only accessible to the investigator who is not masked to treatment. The eyedrops should be stored at room temperature (15-25°C).

Participants and their guardians will be instructed on the administration of eyedrops after recruitment. A 2- or 3-month dosage of eyedrops will be provided at each visit after finishing all the ocular examinations, and all the empty eyedrop containers will be returned at the next visit, to calculate the compliance rate.

The intervention will be discontinued if the guardian or participant requests to withdraw, or participants has severe allergic response, or aggravation of IXT fulfilling the deterioration criteria for two consecutive follow-ups. IXT deterioration criteria will be met by either development of constant exotropia  $\geq 10$  PD at distance and near or presenting with a decrease

in near stereoacuity of at least 2 octaves. When the deterioration criteria are first met, a retest will be performed after a 10-minute break to confirm or refute the result. The participants experiencing deterioration for 2 consecutive follow-ups will be requested to cease the intervention, and then underwent a further two-month observation period. If participants still fulfill the deterioration criteria, surgery will be recommended.

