## **4.2 Secondary objective**

### **4.2.1 Key secondary objective**

To determine the effect of 0.01% atropine eyedrops on exotropia conditions in children with myopia and IXT.

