## **5.6 Sample size**

The sample size is determined using PASS 15 (NCSS, Utah) assuming: (1) the annual reduction of SE as 0.59 D in the 0.01% atropine group and 0.81 D in the control group according to results of the LAMP study; (2) the common standard deviation (SD) is assumed as 0.57 D in each group; (3) randomization to 0.01% atropine group and placebo control group is 2:1. The trial needs 160 participants in the 0.01% atropine group and 80 participants in the control group to provide 80% power (at 5% type I error rate) for detecting a clinically relevant difference of 0.22 D in SE progression at 12 months. To account for an expected drop-out rate of 20% over the 12 months follow-up period, the total number of participants for enrollment is 300 participants (200 in 0.01% atropine group and 100 in placebo control group).

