### **5.9.2 Secondary outcomes**

- 1) Cycloplegic SE change from baseline at 2 years.
- 2) Change from baseline in axial length, monocular function (BCVA, near vision, accommodative amplitude [AA] and photopic/mesopic pupil size), exotropia conditions (distant/near magnitude of exodeviation and distant/near exotropia control), binocular vision (distant/near stereoacuity, near point of convergence [NPC], accommodative convergence/accommodation [AC/A] ratio, and fusional vergence amplitude [FVA]) and safety parameters (intraocular pressure [IOP] and corneal endothelial cell density [ECD]) at 1 year and 2 years.
- 3) Change in choroidal parameters and higher-order aberrations.

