## **7. Statistical analysis**

Statistical analysis will follow intention to treat. Data from children who participate in at least 1 follow-up visit will be included in the analysis. All statistical analyses will be performed using SPSS (IBM Corp, NY, USA) and R (R Foundation for Statistical Computing, <https://www.R-project.org/>). A two-sided *P*-value <0.05 will be considered statistically significant.

Eye-specific outcome measures will be compared between treatment groups using generalized linear models and generalized estimating equations (GEE) will be used to account for inter-eye correlation. Person-level categorical outcomes will be compared between two treatment groups using chi-square test. For comparing the longitudinal changes of outcome measures

between two treatment groups, GEE models with an autoregressive correlation structure will be used. This longitudinal analysis using GEE will include data from all participants including those who withdraw from the trial during the follow-up.

For the change in SE, AL, and choroidal measures, subgroup analyses will be performed for age ( $\leq 8$  years vs.  $> 8$  years), sex (male vs. female), baseline SE ( $\leq -2$  D vs.  $> -2$  D), baseline AL ( $\leq 24$  mm vs.  $> 24$  mm), distant magnitude of exodeviation at baseline ( $\leq 20$  PD vs.  $> 20$  PD) and daily outdoor hours ( $\leq 2$  hours vs.  $> 2$  hours). The differences in treatment effect between subgroups will be evaluated based on the test of interaction between treatment group and subgroup.

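### Exotropia deterioration and the surgery that may follow are defined and acted on but are not outcomes, and no rule covers measurements after surgery, so the key secondary comparison can understate harm or reverse its sign

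*Combined protocol and SAP*

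**What the plan says.** - **Objective.** Section 4.2.1: "To determine the effect of 0.01% atropine eyedrops on exotropia conditions in children with myopia and IXT". The Introduction says that atropine's influence on exotropia and binocular vision is not known, and gives safety as the reason for starting at a relatively low concentration.
- **Outcomes.** Section 5.9.2 measures this objective as change from baseline in "exotropia conditions (distant/near magnitude of exodeviation and distant/near exotropia control") at 1 and 2 years. Stereoacuity is listed under binocular vision. The named safety parameters are intraocular pressure and corneal endothelial cell density. The Synopsis has the same list. Neither deterioration nor surgery appears in either place.
- **Deterioration.** Section 5.8 defines it as constant exotropia of 10 PD or more at both distances, or a loss of near stereoacuity of two octaves or more. Drops are stopped when it is present at two consecutive follow-ups, and two months of observation follow. Then: "If participants still fulfill the deterioration criteria, surgery will be recommended".
- **Analysis.** Section 7 states intention to treat, restricts the data to children with at least one follow-up visit, and adds: "This longitudinal analysis using GEE will include data from all participants including those who withdraw from the trial during the follow-up". It does not mention surgery, and it does not say whether visits continue after drops are stopped or after an operation.
- **Adverse events.** Section 9 treats worsening of a pre-existing condition as a new adverse event. Section 7 plans no comparison of adverse events between arms.

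**The concern.** Deterioration is the event that the protocol regards as serious enough to stop treatment. It can lead to an operation that directly changes deviation and control, the two measures by which the key secondary objective is judged. A child who worsens, is operated on and is then measured can enter the mean as a large improvement. A child who worsens and is no longer measured drops out of the mean because of the outcome itself. If atropine does worsen exotropia, both routes act more often in the atropine arm, and the planned comparison moves away from showing it. At stake is the question that sets this trial apart from earlier atropine trials, which by the Introduction's account excluded children with strabismus.

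**Working it through.** **1. The plan's own figure.** The only sample size given is for the primary outcome. Inputs from sections 5.6 and 7: "the annual reduction of SE as 0.59 D in the 0.01% atropine group and 0.81 D in the control group", so the difference is 0.81 - 0.59 = 0.22 D; "the common standard deviation (SD) is assumed as 0.57 D in each group"; "to provide 80% power (at 5% type I error rate"); two-sided testing; 2:1 allocation; 20% drop-out.

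Control n = (1 + 1/2) x (1.960 + 0.842)² x 0.57² / 0.22² = 1.5 x 7.849 x 0.3249 / 0.0484 = 79.03, rounded up to 80, with 160 on atropine. Power at 80 and 160 is 80.5% (80.2% by the t distribution). Enrolment is 240 / 0.80 = 300. The figure reproduces, and this point does not touch it. There is no corresponding figure for exotropia or deterioration.

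**2. Can surgery fall before the assessments?** Visits are at 2, 4, 6, 9, 12, 15, 18, 21 and 24 months (section 5.10, Table 1). Surgery becomes possible about two months after the second consecutive deterioration.

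| Second deterioration (month) | Surgery possible from (month) |
|---|---|
| 4 | 6 |
| 6 | 8 |
| 9 | 11 |
| 12 | 14 |
| 21 | 23 |

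The first three rows can affect the 12-month value. Anything up to month 21 can affect the 24-month value.

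**3. Direction if post-surgery values are analysed as observed.** Every input here is an assumption. Let pA and pP be the deterioration rates on atropine and placebo, D the rise in PD if not operated, S the fall in PD from baseline after surgery, and u the share of deteriorated children operated on before the assessment, equal in both arms. Other children have mean change zero. Then

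difference in mean change (atropine minus placebo) = (pA - pP) x [D(1 - u) - S x u].

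Positive means worse on atropine. The sign reverses when u > D/(D + S):

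| | S = 10 | S = 20 | S = 30 |
|---|---|---|---|
| D = 3 | 23% | 13% | 9% |
| D = 5 | 33% | 20% | 14% |
| D = 10 | 50% | 33% | 25% |

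With D = 5 and S = 20, the difference in PD is:

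| pA vs pP | u = 0 | u = 50% | u = 75% | u = 100% |
|---|---|---|---|---|
| 15% vs 5% | +0.50 | -0.75 | -1.37 | -2.00 |
| 5% vs 2% | +0.15 | -0.23 | -0.41 | -0.60 |

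**4. Direction if operated children are not measured.** Among those still measured, each arm's mean is p(1 - u)D / (1 - p x u). For 15% vs 5% and D = 5:
- u = 0: +0.50 PD
- u = 50%: 0.375/0.925 - 0.125/0.975 = 0.41 - 0.13 = +0.28 PD
- u = 75%: 0.1875/0.8875 - 0.0625/0.9625 = 0.21 - 0.06 = +0.15 PD
- u = 100%: 0

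Harm shrinks to nothing but does not change sign.

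**5. How strong is the reversal in step 3?** In a simulation with 160 and 80 children, an assumed SD of 6 PD, D = 5, S = 20 and u = 75%, a statistically significant false benefit appeared in about 10% of trials (10% vs 5% deteriorating) and 26% (15% vs 5%).

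If atropine also worsens every non-deteriorated child by m PD, the difference gains (1 - pA) x m. The sign then reverses only while m is below 0.6875/0.90 = 0.76 PD (10% vs 5%) or 1.375/0.85 = 1.62 PD (15% vs 5%).

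**6. Power if deterioration is compared directly** (two-sided 5%; rates assumed):

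| Placebo vs atropine | 100 vs 200 | 80 vs 160 |
|---|---|---|
| 2% vs 5% | 21% | 17% |
| 5% vs 10% | 30% | 24% |
| 5% vs 15% | 75% | 65% |
| 10% vs 20% | 60% | 50% |

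**The case against.** A reader might infer that the plan keeps post-surgery alignment in the analysis, so that the harm question will be answered in the wrong direction and nothing else would reveal it. The documents do not support that much.

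- Section 7 does not say that operated children are still measured or that such values are used. Intention to treat makes that the natural reading, but it is not written. If measurement stops, step 4 applies and harm is hidden rather than reversed.
- Surgery is recommended, not assigned, and only after two consecutive follow-ups and two months of observation. At least two deteriorated visits come before it, and these can enter the longitudinal model.
- Listed outcomes carry some of the signal. Score 5 on the control scale is constant exotropia, and near stereoacuity is one of the two deterioration criteria. Both are measured at every visit. Worsening is also recorded as an adverse event.
- The size is assumed throughout. Eligibility needs only 10 PD at distance, and a planned subgroup is 20 PD or less. In a child with 10-20 PD, a fall of 20-30 PD can exceed the deviation present. Reversal also needs an excess of deterioration on atropine and enough timely operations.

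All of this stands, and it limits the claim. It does not close the gap. Pre-surgery visits do not protect the 1-year and 2-year changes that section 5.9.2 names. Control and stereoacuity, as mean changes, face the same unhandled surgery. Adverse events are recorded without a planned comparison.

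**Conclusion.** The point holds as a gap in the plan. The protocol's own harm event, and the operation that may follow it, are not compared between arms, and the handling of post-surgery measurements is not specified. Depending on how that silence is filled, an excess of deterioration on atropine is diluted, hidden or, under assumed values, reversed in sign. The reversal threshold is 9% to 50% of deteriorated children operated on, for D of 3-10 PD and S of 10-30 PD, when the deterioration rate is the only difference between arms. In the examples the shift is a few tenths of a PD to about 2.5 PD (from +0.50 to -2.00). If surgery is rare the bias is small, but the deterioration event would still go uncompared.

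The documents do not establish that reversal will occur. The primary outcome's sample size is unaffected. This is a should-fix.

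**What to change.** 1. **Section 5.9.2.** Add a secondary outcome: the proportion of children who meet the existing deterioration criteria at two consecutive visits, or have surgery, by 12 and by 24 months. Compare arms by a risk difference with 95% CI. State a rule for drop-outs (section 5.6 expects 20% by 12 months). State another for deterioration first seen at the last visit before a cut-off: an event first seen at month 12 can be confirmed only at month 15, and one first seen at month 24 has no later scheduled visit.
2. **Section 7.** State that visits continue after drops are stopped, and record the date of any surgery; Table 1 has no item for it. For deviation, control, stereoacuity and the other binocular outcomes, do not take post-surgery values at face value in the main analysis. Treat surgery as an unfavourable outcome, for example by a worst-rank composite. Give the as-observed analysis and one using the last pre-surgery values as sensitivity analyses.

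**Cost.** Protocol wording, one added data item and a small amount of extra analysis; the examinations are already scheduled at every visit. A worst-rank result is not a mean in PD, which is why the sensitivity analyses should stand beside it. Power for the deterioration comparison is low unless the excess is large (about 75% for an assumed 5% vs 15% at 100 vs 200), so the interval matters more than the P value. The clinical rules for stopping drops and recommending surgery are not changed.

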## **5.9 Outcomes**

### **5.9.1 Primary outcome**

The primary outcome is cycloplegic SE change from baseline at 1 year.

### **5.9.2 Secondary outcomes**

- 1) Cycloplegic SE change from baseline at 2 years.
- 2) Change from baseline in axial length, monocular function (BCVA, near vision, accommodative amplitude [AA] and photopic/mesopic pupil size), exotropia conditions (distant/near magnitude of exodeviation and distant/near exotropia control), binocular vision (distant/near stereoacuity, near point of convergence [NPC], accommodative convergence/accommodation [AC/A] ratio, and fusional vergence amplitude [FVA]) and safety parameters (intraocular pressure [IOP] and corneal endothelial cell density [ECD]) at 1 year and 2 years.
- 3) Change in choroidal parameters and higher-order aberrations.

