## **5.10 Study visit schedule and procedures**

The participants will undergo a regular assessment every 2 months ( $\pm$  2 weeks)

230 during the first 6 months, followed by assessments every 3 months ( $\pm$  2 weeks)  
231 during the subsequent 18 months. Table 1 shows the visit schedule and study  
232 procedures.

233

234

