| Mesopic/photopic pupil size (OPD-Scan III)                   | √        | √        | √        | √        | √        | √         | √         | √         | √         | √         |
| Intraocular pressure (iCare)                                 | √        | √        | √        | √        | √        | √         | √         | √         | √         | √         |
| Corneal endothelial cell density                             | √        |          |          | √        |          | √         |           | √         |           | √         |

|                                                                                          |   |   |   |   |   |   |   |   |   |   |
|------------------------------------------------------------------------------------------|---|---|---|---|---|---|---|---|---|---|
| (Topcon SP-1P)                                                                           |   |   |   |   |   |   |   |   |   |   |
| Distant/Near magnitude of exodeviation                                                   | √ | √ | √ | √ | √ | √ | √ | √ | √ | √ |
| (Prism and alternate cover test)                                                         |   |   |   |   |   |   |   |   |   |   |
| Distant/near exotropia control (Office-based scale)                                      | √ | √ | √ | √ | √ | √ | √ | √ | √ | √ |
| Distant/Near stereoacuity (Random Dots Distant Test; Randot Preschool Stereoacuity test) | √ | √ | √ | √ | √ | √ | √ | √ | √ | √ |
| Near point of convergence (Near point rule)                                              | √ | √ | √ | √ | √ | √ | √ | √ | √ | √ |
| Fusional vergence amplitude (Synoptophore)                                               | √ | √ | √ | √ | √ | √ | √ | √ | √ | √ |
| Accommodative convergence/accommodation (Far gradient method)                            | √ | √ | √ | √ | √ | √ | √ | √ | √ | √ |
| Dominant eye                                                                             | √ | √ | √ | √ | √ | √ | √ | √ | √ | √ |
| Wavefront aberrometry (Tracey iTrace)                                                    | √ | √ | √ | √ | √ | √ | √ | √ | √ | √ |
| Choroidal structural and vascular component (OCT/OCTA, Optovue)                          | √ | √ | √ | √ | √ | √ | √ | √ | √ | √ |
| Cycloplegic refraction (Topcon KR-8900)                                                  | √ |   |   | √ |   | √ |   | √ |   | √ |

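### The exotropia outcomes for the key secondary objective are compared as raw changes with no baseline covariate and no named contrast; adjusting for the baseline reading would sharpen the 12- and 24-month comparisons at no cost.

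*Combined protocol and SAP*

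**What the plan says.** The key secondary objective (section 4.2.1) is "To determine the effect of 0.01% atropine eyedrops on exotropia conditions in children with myopia and IXT". Section 5.9.2 gives the corresponding outcomes as "exotropia conditions (distant/near magnitude of exodeviation and distant/near exotropia control"), each as a change from baseline at 1 year and at 2 years.

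Section 5.10 sets the visits: "The participants will undergo a regular assessment every 2 months" (with a 2-week window) "during the first 6 months, followed by assessments every 3 months". Table 1 ticks "Distant/Near magnitude of exodeviation" and "Distant/near exotropia control (Office-based scale") at baseline and at 2, 4, 6, 9, 12, 15, 18, 21 and 24 months. That is nine follow-up readings, of which two (12 and 24 months) enter the outcome definitions.

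Section 7 gives three routes:
- generalized linear models with GEE for eye-specific measures;
- chi-square tests for person-level categorical outcomes;
- "For comparing the longitudinal changes of outcome measures" between the arms, GEE with an autoregressive working correlation, including data from children who withdraw.

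No covariates are listed for any of these models. The longitudinal GEE is not tied to particular outcomes, visits or a contrast.

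**The concern.** The introduction (section 3) explains that earlier atropine trials excluded children with strabismus, so the drug's influence on exotropia is unknown. That makes the exotropia comparison the question that most distinguishes this trial, and it deserves a defined and reasonably precise estimate.

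The text falls short in two ways. First, exodeviation is a continuous measure on the child, not on the eye, so neither of the first two routes in section 7 covers it. The longitudinal GEE is the route left, and it has no stated contrast. Second, the outcome is a raw change score and no model carries the baseline value. A raw change contains the full error of the baseline reading as well as that of the follow-up reading. Using the baseline as a covariate removes only as much of it as is predictive. At stake is a wider interval than necessary on a question where an inconclusive result could be taken as reassurance.

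**Working it through.** **The plan's own figure.** Section 5.6 assumes a difference of 0.22 D, SD 0.57 D, 2:1 allocation, 80% power and 5% type I error; section 7 makes the test two-sided. Control-arm n = (1.960 + 0.842)² × 0.57² × (1 + 1/2) / 0.22² = 79.03, rounded up to 80, with 160 on atropine. Power at 160 v 80 is 80.5% by the normal approximation. Allowing for 20% dropout, 240 / 0.80 = 300. All of this reproduces. It concerns the primary outcome only; no figure is given for exotropia.

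**Inputs for the exotropia comparison.**
- From the plan: 160 v 80 children with 12-month data (section 5.6), giving a standard-error factor √(1/160 + 1/80) = 0.1369.
- Assumed: equal SD at baseline and 12 months (set to 1), baseline-to-12-month correlation r between 0.5 and 0.8, and an illustrative effect of 0.30 SD. The documents give none of these.

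**Formulas.** The variance of a raw change is 2(1 − r). The variance of the 12-month value given baseline is 1 − r². Their ratio, adjusted over raw, is (1 + r)/2, so the z-statistic rises by √(2/(1 + r)). Power is Φ(0.30 / (0.1369 × √variance) − 1.96).

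| r | Variance, raw change | Variance, adjusted | z ratio | Power, raw | Power, adjusted |
|---|---|---|---|---|---|
| 0.5 | 1.000 | 0.750 | 1.15 | 59% | 72% |
| 0.6 | 0.800 | 0.640 | 1.12 | 69% | 78% |
| 0.7 | 0.600 | 0.510 | 1.08 | 81% | 87% |
| 0.8 | 0.400 | 0.360 | 1.05 | 93% | 95% |

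Worked line at r = 0.6: the raw standard error is 0.1369 × √0.800 = 0.1225, so z = 2.449 and power = Φ(0.489) = 69%. The adjusted standard error is 0.1369 × √0.640 = 0.1095, so z = 2.739 and power = Φ(0.779) = 78%. The difference detectable with 80% power falls from 2.802 × 0.1225 = 0.343 SD to 2.802 × 0.1095 = 0.307 SD.

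**If the SDs differ.** With baseline SD s0 and 12-month SD s1, the raw-change variance minus the adjusted variance is (s0² + s1² − 2r·s0·s1) − s1²(1 − r²) = (s0 − r·s1)², which is never negative. Apart from the single degree of freedom spent, adjustment does not lose precision.

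**Would averaging over visits be a better outcome?** Take the mean of the 6-, 9- and 12-month readings, adjusted for baseline, with every pair of readings correlated 0.6. Its variance is (1 + 2 × 0.6)/3 − 0.6² = 0.373, and its standard error is 0.1369 × √0.373 = 0.0837.
- Effect of 0.30 SD at all three visits: z = 3.59, power 95%, against 78% for the adjusted 12-month reading.
- Effect starting at 9 months: the mean effect is 0.20 SD, z = 2.39, power 67% against 78%.
- Effect at 12 months only: the mean effect is 0.10 SD, z = 1.20, power 22% against 78%.

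Averaging therefore helps for a constant effect and costs power for a late one. Baseline adjustment carries no such trade-off.

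**The case against.** The strongest reply is that section 7 already plans a longitudinal comparison of outcome measures, that exodeviation and control are outcome measures, and that all nine visits therefore fall within it. This is right. A reader who looks only at section 5.9.2 might infer that seven of nine visits go to waste; section 7 does not support that. Visit-level readings also feed the deterioration rule in section 5.8, although that rule governs discontinuation and is not a comparison between arms.

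A reader might also infer that the GEE will test a group-by-time slope, which suits a drug effect present from the first visit poorly. Nothing in section 7 mentions a slope or linear time; a model with visit as a category fits the wording equally well.

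Change at 1 and 2 years is a legitimate target. It matches the timing of the primary outcome and is easy to read clinically. A reader impressed by the repeated visits might want the outcome redefined as a mean over several of them, but that changes what is estimated and weakens detection of late worsening.

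Finally, an analyst may add the baseline value anyway, and an unstated contrast is on its own only missing detail. Both are fair. But an adjustment chosen after the data are seen is less credible than one written down, and the current text names none.

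**Conclusion.** The point stands as a modest, cost-free gain in precision together with a gap in specification. It is not a finding of unused data or of an invalid analysis. For assumed correlations of 0.5 to 0.8 and 160 v 80 children, baseline adjustment alone multiplies the 12-month z-statistic by about 1.15 down to 1.05; at 0.6, power for 0.30 SD goes from 69% to 78%.

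Larger gains (factors of 1.33 to 1.55) can be calculated by setting a baseline-adjusted multi-visit mean against an unadjusted single change. They combine two separate modifications and assume a constant effect, so they should not be read as the size of this problem.

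The direction of the gain does not depend on the assumptions, but its size does. The correlation and the effect are assumed, and exotropia control is a 0 to 5 ordinal grade, for which standardised-mean power is only approximate. The figures apply to 12 months, since the plan states no 24-month dropout. The primary outcome and the sample size are unaffected.

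**What to change.** Leave the 12- and 24-month outcomes in section 5.9.2 as they are. In section 7, state that for distance and near exodeviation and distance and near control the arm difference is estimated from the planned GEE with treatment, visit as a category, treatment-by-visit, and the baseline value of the same measure as a covariate. State that the 12- and 24-month treatment contrasts, each with a 95% confidence interval, answer the key secondary objective.

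If wanted, pre-specify a treatment contrast averaged over named visits from the same model as a supporting estimate, labelled as such because it dilutes a late effect.

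The cost is a few sentences in the analysis section. No visit, test or child is added, because every baseline value is already scheduled in Table 1.
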